### Intervention

#### RAGT (T-sequence)

Protocols for PBWSTT as well as RAGT in children are very heterogeneous so far. Session frequencies range from 2 to 5 times per week, session durations vary with most studies reporting 20 to 30 min of treadmill walking per session, and length of treatment varies from 2 weeks to 5 months [34]. As our training protocol prescribes the Lokomat training on an outpatient basis, we consider a session frequency of three times per week with a maximum of 45 min of effective walking time on the Lokomat as feasible and a treatment duration of 5 weeks as clinically adequate.

Trained and experienced therapists, who are used to working with children, perform the Lokomat trainings. The trainings are executed following recently published recommendations [34]. Virtual reality scenarios and other available motivating strategies are used in order to increase the child’s adherence to the training. Body-weight support, gait speed as well as guidance force of the Lokomat are individually adjusted according to the child’s abilities and modified within training sessions and during the course over time. To ensure that uniform standards are applied in both centers, a joint practical training session has been performed and the clinical training standards have been discussed beforehand.

Standard therapies can be continued during the intervention period, but should not include specific walking training and not be changed in frequency. Parents list the type as well as the dosage of concomitant therapy in a personal logbook.

#### Usual care (C-sequence)

Usual care normally comprises 1–2 sessions of physiotherapy per week. Hippotherapy, circuit training as well as occupational therapy can also be elements of standard treatment. These therapies, which are individually customized to the needs of the child, are often implemented in the school setting. The content of the usual care treatment does not specifically address gait training, but rather consists of elements addressing range of motion, tone reduction, balance, activities of daily living, etc. Information about the type and dosage of all therapies is documented in a personal logbook by the parents. As the treatment in our study should represent usual care in clinical practice, we refrained from increasing the dosage for the usual care treatment to a comparable level as for the RAGT intervention.

### Descriptive parameters and measures describing the interventions

An overview of all outcome measures and measurement time points is provided in Fig. 2.

To make sure that the therapists from both centers apply common standards, all performed measures have been thoroughly discussed and trained within and between the teams.

Descriptive and clinical data like diagnosis, walking aids, undergone operations, age, height and weight are recorded in order to describe the characteristics of the included patients. A description and quantification of the RAGT sessions is provided by various measures including the percentage of body weight support, gait speed, guidance force, distance walked and the number and duration of training sessions.

### Primary outcome measure

The primary outcome measure is the percentage score of the dimension E (walking, running, jumping) of the Gross Motor Function Measure-88 (GMFM-88). It assesses the gross motor function with regard to walking ability [35]. The GMFM is a well-validated measurement tool for children with CP, which can be regarded as a gold standard for the assessment of gross motor function in children with CP. The dimension E consists of 24 items, each of which is scored on a 4-point ordinal scale. The children perform the test barefoot, or with shoes and orthoses, if orthoses are used when walking indoors in everyday life. The test is performed without walking aids, regardless of the children’s GMFCS-level. A GMFM-certified therapist instructs the children while the test is simultaneously videotaped. These videos are later scored by a blinded rater, who is also a GMFM-certified therapist. The psychometric properties of the total GMFM-88 are well explored in children with CP. Nevertheless, information on single dimensions is rather sparse. There is limited positive evidence for the responsiveness of dimension E, while evidence on reliability is still unknown because of too little patients included in the reliability studies [36]. A recently published study showed that video rating is a reliable option for the dimensions E as well as D with ICCs of 0.992 and 0.965 for the agreement of life and video scores [37].

### Secondary outcome measures

#### GMFM dimension D

The percentage score of the dimension D (standing) of the GMFM-88 to assess the gross motor function with regard to standing ability. The 13 items are carried out and video rated in the same way as described for the dimension E. As for dimension E, there is evidence for responsiveness of dimension D [35]. Reliability seems to be high, but sample sizes of these studies were rather small to allow definite conclusions [35, 38].

#### Six-minute walking test

The 6-minute walking test (6MinWT) is performed on a 30-meter long corridor with poles at each end. The instruction and encouragement of the child follows a standardized test protocol and the covered distance is noted to one meter [39]. Evidence for the test-retest reliability of the 6MinWT is moderate; its responsiveness has not been established in children with CP so far [36].

#### Ten-meter walking test

Gait speed is assessed with the 10-meter walking test (10MWT), which is performed on a 14-meter long track with the child using the walking aid usually used in daily life. The time needed for the middle 10 meters is measured with a stopwatch, allowing 2 meters for acceleration and deceleration each. The test is performed twice without a break. For the evaluation of fast speed (10MWTfast), the child is instructed to walk as fast as possible but without running, from the first to the last line. The faster out of two trials is used for further analysis. For self-selected speed (10MWTss) the child is instructed to walk in a normal, comfortable speed from the first to the last line and the mean of two trials is calculated. All gait tests are performed with orthoses and walking aids usually used in daily life. Evidence for test-retest reliability of the 10MWTfast is moderate in children with CP [36]. To our knowledge, responsiveness of the 10MWTfast as well as psychometric properties of the 10MWTss has not yet been established in children.

#### Measures of body function

Regarding the child’s body function level, range of motion, modified Ashworth scores, and muscle strength by means of manual muscle testing are evaluated in flexion and extension of the hip, knee and ankle joints [40, 41]. These measures will be used for descriptive purposes only.

One complete assessment block takes maximally 120 min.

Additionally, children perform a 3-dimensional gait analysis (3DGA) on an optional basis before and at the end of the intervention period to capture spatio-temporal and kinematic data of the lower body during walking. The Helen Hayes marker set with 16 markers for the lower body, seven infrared Vicon MX cameras (Oxford Metrix Ltd., Oxford, UK) and two floor-mounted force platforms (AMTI OR 6-7-2000, Advanced Mechanical Technology Inc., Watertown, MA, USA) are used for the 3DGA. The mean of six clean force plate strikes for each foot and each parameter of interest is calculated for further analysis to obtain a reliability level of at least 0.9 for each evaluated discrete gait parameter irrespective of the child’s GMFCS level [42].

### Sample size and power calculation

A sample size calculation for a 2×2 cross-over design was performed. It indicated a sample size of 30 to be sufficient to detect a difference of 3.7%-points in the dimension E-score of the GMFM-88 [43], assuming a standard deviation of 6.8%-points [25], a power of 80% and a significance level of 5%. The 3.7%-points represented the cut-off value that best differentiated between great and not great improvement in motor function in children with CP as judged by their therapists [43]. This number has been increased to 34 to allow for a predicted dropout rate of about 10%.

### Statistical analysis

All data are electronically filed by the PI using EpiData software with double data entry and range checks for data values (EpiData Association, Odense, Denmark). The statistical analyses are carried out with SPSS24 (IBM Corporation, New York, USA) and datasets of all study participants are analyzed on an intention-to-treat basis. Descriptive parameters of the participants will be presented. Treatment effects, period effects as well as follow-up effects of the two different treatment interventions are analyzed with paired *t*-tests or Wilcoxon signed-rank tests for paired samples, with the treatment effect being our primary end-point. Unpaired two-sample *t*-tests or Wilcoxon rank sum tests for unpaired samples are used to determine whether carry-over effects are present [44]. Ninety-five percent confidence intervals are presented with a two-tailed level of significance set at *p* < 0.05. The applied analyses are schematically listed in Fig. 3.

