**Fig. 3 Fig3:**
[figure not shown]
Overview of the study protocol and the statistical analyses. Abbreviations: CTC1: Baseline assessment in CTC-group; TC1: Baseline assessment in TC-group; CTC2: Intermediate assessment in CTC-group; TC2: Intermediate assessment in TC-group; CTC3: End assessment in CTC-group; TC3: End assessment in TC-group; CTC4: Follow-up assessment in CTC-group; ∆C1: Change during usual care in CTC-group; ∆C2: change during usual care in TC-group; ∆C3: Change during follow-up in CTC-group; ∆T1: Change during robot-assisted gait training in TC-group; ∆T2: Change during robot-assisted gait training in CTC-group

Subgroup analyses are performed according to impairment level (GMFCS level II vs. GMFCS levels III and IV) and treatment adherence (12 or more training sessions completed vs. less than 12 training sessions), given sufficient numbers within the subgroups.

Missing data will be handled with multiple imputation procedures [45].

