
Although the 5-week follow-up period is rather short, we opted for this time frame because of the increasing risk of confounding factors that is accompanied by a long time interval due to growth, new therapy approaches, illness, operations, increased school load etc.

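### The primary treatment effect is tested with a paired test that carries no period adjustment; period is examined only in a separate test

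*Protocol article*

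**What the plan says.** The Statistical analysis section of the protocol article gives one family of tests for three questions: "Treatment effects, period effects as well as follow-up effects of the two different treatment interventions are analyzed with paired" t-tests or their rank counterpart. It then names the primary analysis: "Wilcoxon signed-rank tests for paired samples, with the treatment effect being our primary end-point". Unpaired tests have a single stated purpose: "Wilcoxon rank sum tests for unpaired samples are used to determine whether carry-over effects are present". Testing is two-sided at 0.05, with 95% confidence intervals.

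The Design and setting section randomises children to sequence: RAGT then usual care (TC), or usual care, RAGT, then usual care as follow-up (CTC). The legend of Fig. 3 defines the changes available: ∆T1 and ∆C2 in the TC group, ∆C1 and ∆T2 in the CTC group. The figure itself is not shown. The Sample size and power calculation section sizes the trial as a 2×2 cross-over, with 30 children "sufficient to detect a difference of 3.7%-points in the dimension E-score of the GMFM-88", an SD of 6.8 points and 80% power. The total is raised to 34 for dropout.

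**The concern.** In a cross-over trial the order of treatments is what is randomised, so each child's RAGT-minus-usual-care difference contains the treatment effect plus or minus any difference between the periods. The sign depends on the sequence. A paired test on all children has no term to separate the two. A separate period test may show that a period effect exists, but it leaves the treatment estimate and its standard error unchanged.

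Two consequences follow if the periods differ. The period difference enters the error term, so the confidence interval is too wide and power is lost even with equal sequences. If the sequences are unequal, part of the period difference also stays in the treatment estimate.

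**Working it through.** **Inputs.** From the article: effect 3.7, SD 6.8, two-sided 5%, 80% power, N = 30. Assumed: the period difference p (change in period 1 minus change in period 2, apart from treatment), over 0 to 5 points. The article gives no value for p.

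**Reproducing the plan's figure.** The article does not say which SD the 6.8 is. As the SD of the within-child difference, the normal approximation gives (2.80 × 6.8 / 3.7)² ≈ 26.5. With the noncentral t distribution, 29 children give power 0.807, and 30 (15 per sequence) give 0.821 for the paired test (29 df) and 0.820 for the two-sample cross-over contrast (28 df). So 30 reproduces. Reading 6.8 as the SD of a single within-child measurement would need about 53 children and does not reproduce. For dropout, 30/0.9 = 33.3, rounded up to 34.

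**Expected differences.** With treatment effect τ, the RAGT-minus-usual-care difference has mean
- TC (∆T1 − ∆C2): τ + p
- CTC (∆T2 − ∆C1): τ − p

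The pooled paired test then has
- mean = τ + p(nTC − nCTC)/N
- expected variance = 6.8² + p² × 4·nTC·nCTC / [N(N − 1)]

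**Equal sequences, 15:15.** At p = 3 the variance is 46.24 + 9 × 900/870 = 55.55, so the SD is 7.45. At p = 5 it is 46.24 + 25 × 900/870 = 72.10, SD 8.49. The confidence interval widens by roughly 7.45/6.80 = 1.10 and 8.49/6.80 = 1.25. Power by simulation:

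| p (assumed) | Paired test | Period-adjusted test |
|---|---|---|
| 0 | 0.82 | 0.82 |
| 2 | 0.80 | 0.82 |
| 3 | 0.77 | 0.82 |
| 4 | 0.72 | 0.82 |
| 5 | 0.66 | 0.82 |

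Simulation is needed because the pooled differences are a mixture of two groups with different means. Treating p as normal noise slightly overstates the loss. With no treatment effect, the paired test rejects about 4.1% of the time at p = 2 and 1.6% at p = 5. The adjusted test stays at 5%.

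**Unequal sequences, p = 3.**
- 16:14: 3 × 2/30 = 0.2 points
- 17:13: 3 × 4/30 = 0.4 points, which is 0.4/3.7 = 11% of the target difference

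The sign follows p(nTC − nCTC), so the bias can favour either treatment. The adjusted estimate has no such bias.

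**If the paired tests were run within each sequence instead.** The TC result estimates τ + p and the CTC result τ − p. Within either sequence alone, treatment and period cannot be separated.

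**The case against.** The strongest reply is that pooling is not stated. The contrasts are listed in Fig. 3, which is not shown, so pooling is inferred from the paired test, the analysis of all participants and the N of 30. That qualification stands. It does not rescue the plan, because the alternative of paired tests within each sequence confounds treatment with period.

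Four stronger readings are tempting, and the article does not support them.

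- *That the plan itself expects a period effect.* The remark on the "increasing risk of confounding factors that is accompanied by a long time interval due to growth" explains why follow-up was kept to 5 weeks. Botulinum toxin appears only as a yes/no minimisation factor, and practice effects are not mentioned. Steady growth adds equally to two 5-week periods and cancels. What the article does show is that a period test was thought worth planning. Values of p of 4 or 5 exceed the target effect and are the far end of the assumed range; at p = 2 the power loss is only about 2 percentage points.
- *That false positives are inflated.* Near balance the test is conservative. At 17:13 and p = 3, type I error is about 4.2%. It rises clearly above 5% only under marked imbalance (7.0% at 20:10 with p = 2), which minimisation with a random factor of 0.9 makes unlikely.
- *That dropout will unbalance the analysis.* All participants are to be analysed by intention to treat, and "Missing data will be handled with multiple imputation procedures", so dropout need not change the numbers analysed per sequence.
- *That a signed-rank test yields no estimate.* A Hodges-Lehmann estimate and interval can accompany it, and how rank tests are combined over imputations is detail an article may leave to the analysis plan.

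**Conclusion.** The point holds as an analysis choice to correct before the primary analysis. The named primary test cannot remove a period difference, and testing for period separately does not repair the estimate. The main harm is lost power and an interval that is too wide: at N = 30 and 15:15, power falls from 0.82 to 0.77 at p = 3 and to about 0.66 at p = 5. Bias is secondary, at 0.2 to 0.4 points for 16:14 to 17:13 with p = 3.

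These sizes rest on an assumed p, on 6.8 being the SD of the within-child difference, and on the inference that the test is pooled over both sequences. If p is zero, little is lost. A reader might infer that the sample size of 30 is wrong or that the trial is likely to give a false positive result; neither follows.

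**What to change.** Make the primary test a two-sample t-test between sequences of each child's first-period change minus second-period change, with the difference in means halved. This quantity has mean τ + p in TC (∆T1 − ∆C2) and −τ + p in CTC (∆C1 − ∆T2). The difference between sequences is 2τ, and p cancels whatever the group sizes. An equivalent mixed model, with treatment and period as fixed effects and child as random effect, serves as well. The two changes share the middle assessment with opposite signs, so the model must allow a negative within-child correlation if it is to be equivalent. Keep the rank-sum version as a sensitivity analysis, and bring Fig. 3 into line.

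The cost is a change of wording and one degree of freedom (28 instead of 29; power 0.820 against 0.821 at p = 0). The sample size does not change. Carry-over, which the Discussion accepts as a risk of having no washout, is a separate matter that this change does not address.

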## Discussion

RAGT was implemented in the clinical setting of the two participating pediatric neurorehabilitation centers as innovative therapeutic approach almost 10 years ago. It has become an established treatment option in these clinics to address gait impairments in the in- as well as outpatient setting despite the fact that evidence for its effectiveness is vague. As we want to determine the effects of RAGT as it is applied in the clinical setting, we designed this pragmatic trial. The pragmatic trial design allows to evaluate the effects of an intervention under the usual conditions in which it is applied, whereas explanatory trials determine the effects of an intervention under ideal circumstances [46]. Thorpe et al. defined a pragmatic-explanatory continuum, an instrument to determine the extent to which a trial can be viewed as pragmatic or explanatory [46]. Our trial addresses most domains at the rather pragmatic end of this continuum. We make concessions towards a more explanatory approach in two domains: Regarding the flexibility of the experimental design, we standardize frequency, timing and duration of the RAGT intervention and impose some restrictions regarding the co-interventions. A further domain concerns the primary outcome assessment: While we use the dimension E of the GMFM-88, which is a standard outcome in our clinics as well as for the assessment of gross motor functions in children with CP, we deviate from a clear pragmatic approach by videotaping the assessments and including an additional follow-up assessment. We are confident that the chosen trial design allows the evaluation of the effects of RAGT as it is implemented in the daily routine of our clinics, while keeping the additional burden for the participating children and their families as low as possible. This is also the reason why we perform the follow-up assessment only in one group. As participation in this trial still requires a considerable amount of time, we expect some difficulties in recruitment. The study is therefore carried out in two centers, namely the only two centers in Switzerland that offer a pediatric Lokomat training on a regular basis so far. In addition, we designed the study as a cross-over trial. The strength of this design is that each child receives both treatments, but in a random order. Thus, each patient can act as his or her own control requiring only half the number of patients needed in a parallel group design. As variation within a person is usually less than between patients the treatment effect can be estimated with higher precision despite smaller sample sizes [44]. On the other hand, a disadvantage of the cross-over design is the risk of possible carry-over effects, which means that the effect of the treatment in the first period has an effect that lasts into the second period. A carry-over effect leads to an underestimation of the effect of the treatment in the second period. By introducing a washout period between the different treatment periods, this risk could be reduced. Introducing a washout period would lead to an additional assessment. In order to reduce the load of the participants to a minimum we abstained from a washout period being aware that this might influence our results.

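### The unpaired carry-over test, with about 15 children per sequence and no washout, cannot show that carry-over is absent; report fading as an estimate, beside a first-period comparison.

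*Protocol article*

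**What the plan says.** Under Statistical analysis, the treatment effect is the primary end-point and is tested with paired t-tests or signed-rank tests. For carry-over, unpaired two-sample t-tests or "Wilcoxon rank sum tests for unpaired samples are used to determine whether carry-over effects are present". The only level given is a "two-tailed level of significance set at" p < 0.05, with 95% confidence intervals. The exact contrasts are referred to Fig. 3, which is not shown; its legend defines the single-period changes ∆T1, ∆T2, ∆C1, ∆C2 and ∆C3.

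Under Sample size and power calculation, the figure is for a 2×2 cross-over: "It indicated a sample size of 30 to be sufficient to detect a difference of 3.7%-points in the dimension E-score of the GMFM-88", "assuming a standard deviation of 6.8%-points", with 80% power at the 5% level. "This number has been increased to 34 to allow for a predicted dropout rate of about 10" per cent. No power is given for the carry-over test.

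The Discussion grants that "a disadvantage of the cross-over design is the risk of possible carry-over effects", describes it as making the second-period treatment look less effective than it is, and says that a washout was left out to limit the load on families, in the knowledge that this could affect the results.

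**The concern.** In the TC-group, usual care starts straight after RAGT. If the RAGT gain fades in those five weeks, the loss is counted as a poor result of usual care, and the paired treatment difference grows. By the Discussion's own description the second-period treatment is understated, and in the TC-group that treatment is the control. Fading therefore biases the primary estimate towards RAGT.

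The plan's stated tool for deciding whether this has happened is a between-group significance test in a trial sized for a within-child comparison. If the test has little power for fading that matters, non-significance is a likely outcome whether or not carry-over exists, and it says little about bias in the primary result.

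**Working it through.** **Inputs.** From Sample size and power calculation: effect 3.7, SD 6.8, N = 30 evaluable and 34 recruited, 80% power, 5% level. From Statistical analysis: unpaired test, two-sided. Assumed: 1:1 allocation (no ratio is stated), so 15 per sequence, or at most 17 with no dropout; equal variances of the two period changes; and the conventional carry-over contrast, each child's sum of the two period changes.

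**1. The plan's own figure.** Paired t-test with SD of the within-child difference 6.8: non-centrality (3.7/6.8) × √30 = 2.98. Power is 80.7% at n = 29 and 82.1% at n = 30. Dropout: 30/0.90 = 33.3, so 34. The stated numbers reproduce. They do so only if 6.8 is the SD of the within-child treatment difference; read as a within-subject SD it gives 54 in total, and as a parallel-group SD 54 per arm.

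**2. Bias from fading.** Let c be the usual-care change, τ the RAGT advantage, and L the gain lost in the TC-group's later usual-care period.
- TC: ∆T1 = c + τ and ∆C2 = c - L, so difference τ + L and sum 2c + τ - L.
- CTC: ∆C1 = c and ∆T2 = c + τ, so difference τ and sum 2c + τ.

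With equal groups the mean paired difference is τ + L/2, and the sums differ by L. For τ = 3.7, L = 1.85 (half the gain lost) inflates the estimate by 0.925/3.7 = 25%; L = 3.7 (all of it lost) inflates it by 1.85/3.7 = 50%.

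**3. Power of the between-sequence test if the SD of the sum is 6.8.** SE = 6.8 × √(2/15) = 2.48. Non-centrality is 1.85/2.48 = 0.745 or 3.7/2.48 = 1.49, against a critical t (28 df) of 2.048. Power is 11.1% and 30.2%. Simulated rank sum tests give 10.0% and 27.7%. Power reaches about 82% only at L = 7.4, twice the target effect. The 95% interval has half-width 2.048 × 2.48 = 5.1 points, more than the target effect.

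**4. Dependence on the unstated SD.** With the SD of the difference held at 6.8 and correlation ρ between a child's two period changes, SD of sum = 6.8 × √((1 + ρ)/(1 - ρ)).

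| ρ | SD of sum | L = 1.85, 15 (17) per sequence | L = 3.7, 15 (17) per sequence |
|---|---|---|---|
| +0.5 | 11.78 | 7% (7%) | 13% (14%) |
| +0.25 | 8.78 | 9% (9%) | 20% (22%) |
| 0 | 6.80 | 11% (12%) | 30% (34%) |
| -0.25 | 5.27 | 15% (17%) | 46% (51%) |
| -0.5 | 3.93 | 24% (27%) | 70% (76%) |

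The last row is what independent error at each visit would give, because both changes share the middle assessment. No cell reaches 80%.

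**5. Another possible contrast.** If the hidden figure compares only ∆C1 with ∆C2, the SD at ρ = 0 is 6.8/√2 = 4.81 and power with 15 per sequence is 18% and 53%.

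**The case against.** The strongest reply is that no single power figure belongs to this plan. The SD of the between-sequence contrast is not given, and the planning SD applies to it only if the two period changes are uncorrelated. A negative correlation is plausible, and at -0.5 the test would find total loss of the gain in 70% of trials. The contrast itself sits in a figure not shown, and the 25-50% inflation range is a choice made for this check. All of this stands, so 11-30% must be read as conditional, and it would be wrong to say that the test fails in most trials for every amount of fading. The conclusion survives because power is below 80% in every case examined.

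A reader might also call the test the only safeguard. It is not. The CTC-group returns to usual care after RAGT, and ∆C3 is tested within child. With 15 children and a per-period SD of 4.81 (ρ = 0), non-centrality L × √15/4.81 gives about 28% and 79% power for losses of 1.85 and 3.7. That is direct evidence on fading, but it comes from half the children, has no concurrent control, and does not correct the primary estimate.

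A reader might infer that the test selects the analysis, so that a two-stage procedure distorts the type I error, or that the authors will treat non-significance as proof of no carry-over. The article states neither. It acknowledges that omitting the washout may matter, and it promises confidence intervals. What stands against it is narrower: the stated purpose of the test is a presence-or-absence decision that the data cannot support.

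**Conclusion.** The point holds in this form: an unpaired 5% test with about 15 children per sequence is given the task of determining whether carry-over is present, and a non-significant result cannot establish that it is absent. For fading that inflates a 3.7-point effect by 25%, power is 7-24%; for 50% inflation it is 13-70%. At the planning SD the figures are 11% and 30%. Seventeen per sequence does not change the conclusion.

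This rests on 1:1 allocation, equal variances of the two period changes, 6.8 as the SD of the within-child difference (the only reading that reproduces N = 30), and the sum of period changes as the contrast. It is a matter of analysis and interpretation that should be corrected. It does not show that carry-over will occur or that the primary result is biased.

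**What to change.** 1. Do not use the test as a yes/no determination. Report the between-sequence difference with its 95% confidence interval as an estimate of how much RAGT gain is lost, alongside ∆C3 in the CTC-group.
2. Always report the first-period comparison, ∆T1 versus ∆C1 adjusted for the first assessment, next to the cross-over estimate, whatever the carry-over result. It precedes any crossing over and so is free of carry-over.
3. State that a non-significant carry-over test is not evidence of no carry-over.

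Cost: a few sentences and a little more analysis, using assessments already scheduled and no further children. The first-period comparison is less precise. At ρ = 0 and before baseline adjustment its standard error is 4.81 × √(2/15) = 1.76, against 6.8/√30 = 1.24 for the cross-over estimate, so it should stand as a companion to the primary result and not replace it.

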### Randomization, allocation concealment, and blinding

Randomization into the two groups with different intervention sequences is performed using a minimization method with a random factor of 0.9, including the factors severity of impairment (GMFCS-level II or III/IV), age (6–11 years or 11–18 years) and Botulinum Toxin A-treatment (present or absent) in the preceding 6 months. Minimization facilitates balancing even small groups in terms of selected patient factors at all stages of a trial. To ensure that group allocation is concealed for patients and their families as well as everyone who is involved at any stage of the trial, the randomization list is generated by a person not belonging to the study team on www.randomizer.at and stored off site. Directly after inclusion of the patient the principal investigator (PI) seeks information about group allocation through a phone call or an e-mail. As soon as a child is allocated to one of the two groups, the assessments and trainings are planned according to the assigned intervention sequence, taking into account as much as possible the families’ requests and the school schedule of the child.

The rater of the primary outcome and parts of the secondary outcomes is blinded as the performance of the child in these tests is video recorded and scored by means of these videos with the rater being unaware of the date the video has been recorded. The same applies to the statistician.

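### The carry-over test ignores the three factors used to minimise allocation, so it is conservative if those factors predict the compared quantity (minor)

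*Protocol article*

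**What the plan says.** The Randomization section of the protocol article assigns children to the two sequences "using a minimization method with a random factor of 0.9". Three factors enter it: GMFCS group (II against III/IV), age band, and whether botulinum toxin was given in the previous half-year. The stated reason is that "Minimization facilitates balancing even small groups in terms of selected patient factors at all stages of a trial".

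The Statistical analysis section names two kinds of test. Treatment, period and follow-up effects are tested within child, by paired t-tests or "Wilcoxon signed-rank tests for paired samples, with the treatment effect being our primary end-point". Carry-over is tested between the sequences, by unpaired t-tests or "Wilcoxon rank sum tests for unpaired samples are used to determine whether carry-over effects are present". No covariate is named for either kind. Of the minimisation factors only GMFCS returns in the analysis, and only to define a subgroup: "Subgroup analyses are performed according to impairment level (GMFCS level II vs. GMFCS levels III and IV"), subject to sufficient numbers.

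The Discussion explains that a washout period was left out to spare the families a further assessment. It accepts that carry-over could affect the results and says that carry-over would lead to underestimation in the second period.

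**The concern.** Minimisation removes most of the chance imbalance between TC and CTC on the three factors, so the difference between sequences varies less from one possible allocation to another than it would under simple randomisation. The plain two-sample test does not use this. Its standard error is built from the full spread within each sequence, including the part due to GMFCS, age and botulinum toxin. If that part is not zero, the reported interval is too wide and the test rejects less often than its nominal level.

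For a carry-over check the harmful error is a miss, and a conservative test makes misses more likely. With no washout, this is the only check on carry-over that the section names.

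**Working it through.** **Inputs from the protocol article.** Minimisation with random factor 0.9 on three two-level factors; two sequences; 30 children evaluable and 34 recruited; two-sided 5% level; detectable difference 3.7 and SD 6.8 percentage points.

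**Inputs assumed.** The documents give no R² for the three factors, so a range from 0 to 0.50 is used. Factor prevalences of 50%, 50% and 30% are also assumed. The simulations use the t-test form of the carry-over test.

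**1. The plan's own sample size.** The article states "A sample size calculation for a 2×2 cross-over design was performed" and finds "a sample size of 30 to be sufficient to detect a difference of 3.7%-points in the dimension E-score of the GMFM-88". Taking 6.8 as the SD of the within-child difference, the normal approximation is ((1.960 + 0.842) × 6.8 / 3.7)² = 26.5, that is 27. The noncentral t gives 29 (power 80.7%), and an even total for two sequences gives 30 (power 82%). For dropout, 30 / 0.9 = 33.3, that is 34. Both figures reproduce, and nothing below alters them.

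**2. Expected size of the effect on the carry-over test.** In SD units with 17 children per sequence, the two-sample standard error is √(1/17 + 1/17) = 0.343, whatever R² is. If minimisation balanced the factors perfectly, the true standard error would be 0.343 × √(1 − R²): 0.325 at R² = 0.10, 0.297 at 0.25 and 0.243 at 0.50.

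**3. Simulation with the actual minimisation rule, N = 34.** Minimisation at 0.9 leaves a little imbalance, so the true standard errors tend to lie slightly above those ideal values. Ranges are over repeat simulations.

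| R² | Unadjusted SE | True SE | True level, nominal 5% | Power, 0.8 SD, unadjusted | Power, 0.8 SD, adjusted |
|---|---|---|---|---|---|
| 0.10 | 0.34 | 0.326 | 3.9–4.5% | 63% | 65–66% |
| 0.25 | 0.34 | 0.296–0.304 | 2.3–2.7% | 63–64% | 73–74% |
| 0.50 | 0.34 | 0.257–0.258 | 0.9–1.1% | 64% | 88–89% |

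The adjusted test stayed close to its nominal level (4.4–5.6%).

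**4. Low end of the range.** At R² = 0 and N = 34, power for 0.8 SD is about 61% with or without adjustment. At R² = 0.05 the unadjusted level is 4.9%, and the adjusted interval is 1.5% narrower (ratio 0.985).

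**5. Same check at N = 30.** The unadjusted standard error exceeds the true one by 0.362/0.346 = 1.05 at R² = 0.10, 0.362/0.331 = 1.09 at 0.20, 0.363/0.318 = 1.14 at 0.30 and 0.364/0.278 = 1.31 at 0.50. The adjusted interval is 4%, 10%, 16% and 29% narrower respectively. At R² = 0 it is 1.3% wider, which is the price of three degrees of freedom.

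**6. The primary paired contrast.** A factor that shifts both of a child's change scores equally cancels in the difference between them. In simulation at N = 30, the paired standard error is 1.23 points whether each factor shifts the change scores by 0, 5 or 10 points. For comparison, 6.8/√30 = 1.24. There is nothing to recover there.

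**The case against.** The strongest reply is that the effect is probably small. The legend of Fig. 3 defines the analysed quantities as changes, and the figure itself is not shown, so a carry-over test on raw dimension E scores cannot be assumed. For change scores R² may well be 0.10 or less, and the gain is then about two to three points of power. The error is also in the safe direction for false positives: type I error is not inflated and the treatment estimate is not biased. The section attaches no decision to the carry-over test, and the check would remain weak at this sample size. A full analysis plan may also name covariates. Most of this stands and is why the point is minor. It does not remove the point, because the article states which test will be used, that test does not match the stated allocation, and adjustment costs almost nothing even when the factors are irrelevant.

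A reader might go further and infer that the primary treatment contrast also loses precision. The argument would be that if the RAGT effect differed by 3 to 5 points between GMFCS groups, the factor would account for (1.5/6.8)² = 4.9% to (2.5/6.8)² = 13.5% of the variance, and covariates would remove it. The documents do not support this. A subgroup analysis subject to numbers states no expectation of such a difference, and the 3-to-5-point gap is an outside assumption set against a target effect of 3.7. The statistics do not support it either. With centred covariates the intercept is exactly the unadjusted mean difference, so the estimate does not change. Only the printed standard error shrinks (1.16 to 1.08 for a 5-point gap at N = 34), while the true standard deviation of the estimate stays at 1.16. Type I error for the average effect then rises to 5.4% for a 3-point gap and 6.7% for a 5-point gap.

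**Conclusion.** The point holds for the carry-over test alone, and it is minor. That test ignores the factors on which allocation was balanced, and it is conservative to the extent that they predict the compared quantity. At N = 34 the loss is negligible for R² up to 0.05 and small at 0.10. At 0.25 it is about nine points of power for a 0.8-SD difference, and at 0.50 about 25 points, though so high a value is unlikely for change scores. These sizes rest on an R² and factor prevalences that the documents do not give.

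It would be wrong to read this as a fault in every planned test. As described, the treatment, period and follow-up tests are paired within child, and no change to them or to the sample size is called for. The point keeps some weight because washout was omitted and no other carry-over check is named.

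**What to change.** In the Statistical analysis section, replace the plain unpaired carry-over test with a linear model for the same compared quantity. It should contain sequence plus GMFCS group, age band and botulinum toxin treatment, coded as they were at allocation. Report the sequence coefficient with its 95% confidence interval. Leave the paired tests as they are.

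The cost is one sentence and three degrees of freedom. All three factors are already recorded at allocation, so no new data, assessments or children are needed.
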